# Does a simplified algorithm and integrated HCV care model improve linkage to care, retention, and cure among people who inject drugs? A pragmatic quality improvement randomized controlled trial protocol

**DOI:** 10.1186/s12879-024-08982-1

**Published:** 2024-01-19

**Keywords:** Hepatitis C, Hepatitis C treatment, People who inject drugs, Mobile medical clinic, People experiencing homelessness, Treatment initiation, Linkage to care, Quality improvement

## Abstract

**Background:**

As many as 2.4 million Americans are affected by chronic Hepatitis C Virus (HCV) in the United States.In 2018, the estimated number of adults with a history of HCV infection in San Diego County was 55,354 (95% CI: 25,411–93,329). This corresponded to a seroprevalence of 2.1% (95% CI: 2.1–3.4%). One-third of infections were among PWID. Published research has demonstrated that direct-acting antivirals (DAAs) have high efficacy and can now be used by primary care providers to treat HCV. In addition, limited evidence exists to support the effectiveness of simplified algorithms in clinical trial and real-world settings. Even with expanded access to HCV treatment in primary care settings, there are still groups, especially people who inject drugs (PWID) and people experiencing homelessness, who experience treatment disparities due to access and treatment barriers. The current study extends the simplified algorithm with a streetside ‘one-stop-shop’ approach with integrated care (including the offer of buprenorphine prescriptions and abscess care) using a mobile clinic situated adjacent to a syringe service program serving many homeless populations. Rates of HCV treatment initiation and retention will be compared between patients offered HCV care in a mobile clinic adjacent to a syringe services program (SSP) and homeless encampment versus those who are linked to a community clinic’s current practice of usual care, which includes comprehensive patient navigation.

**Methods:**

A quasi-experimental, prospective, interventional, comparative effectiveness trial with allocation of approximately 200 patients who inject drugs and have chronic HCV to the "simplified care" pathway (intervention group) or the "usual care" pathway (control group). Block randomization will be performed with a 1:1 randomization.

**Discussion:**

Previous research has demonstrated acceptable outcomes for patients treated using simplified algorithms for DAAs and point-of-care testing in mobile medical clinics; however, there are opportunities to explore how these new, innovative systems of care impact treatment initiation rates or other HCV care cascade outcomes among PWID.

**Trial registration:**

We have registered our study with ClinicalTrials.gov, a resource of the United States National Library of Medicine. This database contains research studies from United States and other countries around the world. Our study has not been previously published. The ClinicalTrials.gov registration identifier is NCT04741750.

## Background

With as many as 2.4 million Americans affected by chronic Hepatitis C Virus (HCV) [1], it is one of the most common blood-borne diseases in the United States [1]. There are numerous studies assessing cascades of care for dried blood spot and point of care testing in different settings including in prisons, community and mobile units [2, 3]. Reports of new infections have increased for the seventh consecutive year, with 44,300 new HCV infections in 2017—a 7.5% increase from 2016 and a 375% increase since 2010 [4, 5]. Nationwide, rates of new infections have risen dramatically among young adults in their 20s and 30s [4], the same cohorts most affected by the opioid epidemic, with as many as 70% of new infections related to injection drug use [5]. Local/regional rates of new infection mirror these national surveillance findings. In 2018, the estimated number of adults with a history of HCV infection in San Diego County was 55,354 (95% CI: 25,411–93,329). This corresponded to a seroprevalence of 2.1% (95% CI: 2.1–3.4%). One-third of infections were among PWID.” [6]. Expanded prevalence estimates indicate a population prevalence rate for HCV of 2.0% to 2.7% in San Diego County, suggesting that approximately 65,000 to 88,000 individuals in the region are likely HCV-infected, with these infections concentrated in the PWID population, with an estimated 65% seroprevalence [6].

These alarming increases in new HCV infections and very high seroprevalence in PWID demand effective treatment delivered to populations that have historically been difficult to reach and, due to a constellation of barriers to care, are characterized by disparities in HCV screening, linkage to care, and treatment access. Advances in HCV treatment and care (e.g., the development of highly effective direct-acting antivirals—DAAs) show promise for treating these populations and have led to worldwide HCV elimination goals [7], as well as local/regional elimination campaigns—with Family Health Centers of San Diego’s (FHCSD) Hepatitis treatment team providing elimination leadership through the county-wide End Hep C San Diego Initiative. While the American Association for the Study of Liver Diseases/Infectious Diseases Society of America (AASLD/IDSA)’s guidelines have long been considered the gold standard for Hepatitis C (HCV) diagnosis, workup, and treatment (and remain appropriate for HCV specialists, especially in complex cases of HCV infection) recent World Health Organization (WHO) HCV guidelines [8] and published consensus statements [9] call for implementation of streamlined and simplified algorithms for HCV care, delivered in an integrated primary care setting. They highlight that most patients, particularly younger people who inject drugs (PWID), have a low risk of cirrhosis and do not require genotyping if treated with pangenotypic regimens. Furthermore, emerging evidence indicates that PWID have been able to achieve high cure rates relative to their high transmission risk. Therefore, it is critical to make concerted efforts to target these patient populations to achieve HCV elimination [10–12]. While these findings offer a hopeful outlook for treatment, many of these patients may be lost to follow-up due to overly complex, time-intensive, and costly evaluations [10].

While research indicates that DAAs have high efficacy and safety and can now be used by primary care providers to treat HCV [13–15], limited evidence exists to support the safety and effectiveness of simplified algorithms, nor patient uptake and efficiency of the approach in a real-world setting. For example, even with expanded access to HCV treatment in primary care settings, there are still groups, especially PWID and people experiencing homelessness, who experience treatment disparities due to access and treatment barriers [16]. In particular, those who are pre-contemplative with respect to medications for opioid use disorder, actively injecting drugs and street homeless, transportation needs and competing priorities serve as major barriers to accessing testing and treatment for HCV. In response to this need, new and innovative methods to simplify the care cascade and expand screening and treatment access are being introduced, including use of mobile medical clinics.

At least one study has shown that point of care testing in a mobile medical clinic resulted in significantly higher rates of HCV infected patients being linked to HCV treatment in 30 days compared to standard phlebotomy HCV testing [17]. While simplified HCV diagnostic and treatment algorithms have shown promise in improving treatment initiation and completion rates [9–11, 18, 19], studies have largely been confined to the traditional clinic environment. The current study combines the simplified treatment algorithm with streetside treatment as the point of service of our syringe service program (SSP) thus exploring a novel, patient-centered approach. Therefore, the proposed study will test the effectiveness of a simplified HCV algorithm with integrated care (including the offer of buprenorphine prescriptions and abscess care), in a street-based mobile clinic setting among PWID and people experiencing homelessness, in increasing treatment initiation and retention rates. Rates of HCV treatment initiation and retention will be compared between patients managed using a simplified algorithm of HCV care in a mobile clinic versus those who are linked to FHCSD’s community clinic current practice of usual care, which includes comprehensive patient navigation.

The primary objective of this Hepatitis C pragmatic quality improvement comparative effectiveness trial is to determine the effectiveness of using a simplified HCV algorithm coupled with integrated care for PWID, delivered in a mobile medical clinic, to increase the number of patients who initiate treatment compared to a concurrent control group receiving usual care.

The secondary objectives are to determine if the simplified algorithm and mobile treatment delivery results in improvement of: (1) HCV therapy completion; (2) SVR12 rates; (3) initiation rates for Medication Assisted Treatment (MAT) for opioid use disorder; (4) persistence on MAT; and (5) receipt of abscess care. Additional exploratory aims are to determine the average time to linkage to care and HCV treatment initiation (and other HCV care cascade outcomes) and compare these times to a similar historical sample. Data to be generated from this study includes the number of patients with chronic HCV who are linked to care, start DAA therapy, complete therapy, return for SVR12, and attain SVR12. Data also will be collected on general engagement in care, initiation of MAT, and abscess care. Results will provide a fuller understanding of the impact of innovative elimination strategies through simplification of the HCV patient care cascade. Results also will have policy implications for payer regulations concerning the safe, effective, and efficient treatment of HCV, as well as clinical implications for innovative ways to engage marginalized patients.

## Methods/design

This study is a quasi-experimental, prospective, interventional, comparative effectiveness trial with random allocation of approximately 200 patients who inject drugs and test positive for HCV Ab to one of two groups. One group receives the “simplified care” pathway (intervention group), while the other group of patients receives the “usual care” pathway (control group). The design of the trial and flow of patients are shown in Fig. 1.

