### Sample size justification

To ensure that the proposed study has adequate power to determine the effectiveness of the simplified algorithm to determine the effectiveness of the simplified algorithm to improve HCV treatment initiation, i.e., the percentage of patients who are HCV RNA positivie and initiate treatment, the sample size was calculated based on a two-sided, two-sample proportion test with 80% power at a significance level of 5%. According to existing FHCSD data, between 20-25% of HCV infected patients (HCV RNA positive) initiate care [20]. Because the proposed treatment strategy addresses both barriers and facilitators of HCV treatment initiation, we believe that a greater than 15-20% improvement in care initiation is achievable. Thus, when the proportion of patients who initiate treatment in the control group is 20%, the target sample of approximately 200 patients (100 per study group) will provide sufficient power to detect a difference of approximately 17.5%. Furthermore, existing FHCSD data indicates that in the syringe exchange setting, approximately 15-20% of patients who take a rapid finger stick test are HCV Ab positive and of those, roughly 75% are HCV RNA positive [21]. Therefore, we will aim to administer approximately 1,350 tests during patient recruitment in order to identify approximately 200 patients who are HCV RNA positive and will be offered treatment.

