### Recruitment

Patients are recruited from FHCSD's mobile SSP population (N >2,369). Data from a survey of SSP clients shows that 94% of the population is low income, 70% are homeless or unstably housed, and 78% have co-occurring mental health and/or substance use disorders. 90% are uninsured or covered by Medi-Cal. Patients are potentially eligible to participate in the study and excluded if they are age <18 years, and have one or more of the following: undetectable HCV RNA, a life expectancy of < 6 months, known clinical or laboratory characteristics indicating decompensated cirrhosis, known hepatocellular carcinoma. Additionally, they are excluded if they are pregnant.

Patients are recruited and enrolled in the study once or twice a week (Tuesdays and or Thursdays) for 30 months. We expect to stop enrollment in September 2023.

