### Intervention

The interventions consist of 12 weeks of HCV treatment and 12 weeks of follow-up. The experimental group (“simplified care,” *n* = 100) will consist of patients who will be offered a simplified HCV workup, Medication Assisted Treatment (MAT), and abscess care to meet patients’ urgent and survival needs while capitalizing on the ability to initiate HCV therapy when they are most motivated to engage in care. A complete HCV workup will be offered immediately upon a preliminary positive HCV Ab test at a mobile medical clinic parked adjacent to the mobile SSP van, or at a second homeless tent site located several blocks from the SSP van. On-site workup will include: CBC, CMP, INR, HCV RNA, HBV serologies, a point of care HIV test, and point of care liver fibrosis measurement (Fibroscan mini). HCV genotype also will be drawn if required by the patient’s insurance prior authorization requirements.

Patients will be assessed for opioid use disorder and, if appropriate, will be offered 7-day starter packs of buprenorphine/naloxone and linkage into FHCSD’s MAT program. Concurrently, patients will receive skin infection and abscess care if needed. Upon completion of the 20-minute visit, patients will have undergone a workup sufficient to initiate a prior authorization request for DAAs from their payer and an appointment for full-scope MAT follow-up in an FHCSD clinic if indicated. Rapid HCV blood tests, patient coordination, authorization efforts with insurance companies, and scheduling of appointments, follow-up, and ancillary support services will be conducted by the HCV Patient Navigator who will provide continuity of patient care which is expected to foster high rates of patient linkage to, and retention in, HCV care. Confirmatory HCV tests and other needed blood tests will be performed by the Certified Phlebotomy Technician. Blood samples will be transported to FHCSD’s centralized laboratory for processing.

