The concurrent control group (“usual care,” *n* = 100) will receive treatment consistent with FHCSD’s current practice. Patients with a positive HCV Ab rapid finger stick test will have immediate phlebotomy performed for HCV RNA. Results will be disclosed the following week upon a second visit and HCV RNA positive patients will be offered referrals and assisted with comprehensive patient navigation to attend an initial HCV evaluation at an HCV-treating FHCSD clinic. At patients’ first visit after linkage to an FHCSD clinic, baseline CBC, CMP, chronic Hepatitis panel, HCV Genotype (if required), Hepatitis A Ab, and INR tests will be performed. Another visit will be required to conduct Fibroscan/SWE, and another separate visit will be required to perform abdominal ultrasound. When a full workup is completed, the prior authorization request will occur as per usual FHCSD clinic-based process. As in the intervention group, HCV treatment regimens will be selected according to current ASSLD/IDSA guidelines (www.hcvguidelines.org) and insurance preference. When DAA medications are approved and delivered (typically a month after the preliminary positive HCV Ab rapid finger stick test), patients can begin treatment. Patients will be seen at week #2, 4, 8, and 12 as per usual FHCSD practice. In the fourth treatment week, HCV RNA and CMP tests will be conducted. At the end of treatment (either 8th or 12th treatment week), end-of-treatment HCV RNA and CMP tests will be conducted. Twelve weeks after treatment is completed, an SVR12 HCV RNA and CMP tests will be conducted. As in the experimental group, an HCV Patient Navigator will conduct patient coordination, assist with prior authorization efforts with insurance companies, schedule follow-up appointments, and attempt to alleviate other barriers. The HCV Patient Navigator will extract test results from the electronic medical record and enter them into a study database; disclose confirmatory test results to the patient; conduct post-test counseling; provide educational materials, address barriers to attending medical appointments, and schedule medical visits. Throughout treatment, CMIS will trigger reminders to contact patients for appointments and the HCV Patient Navigator will contact patients and address barriers to treatment, as needed. In the case of missed appointments, the HCV Patient Navigator will reach out to patients to reschedule appointments and address barriers. Patients in need of buprenorphrine/naloxone, MAT, skin infection treatment, and abscess care will have access to these services as is current practice within FHCSD’s fixed-site clinic site.

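### The protocol counts its 200 patients as antibody-positive in one place and RNA-positive in others; if only 200 antibody-positive patients are randomised, power is about 62–67%, not 80%

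*Protocol article*

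**What the plan says.** The protocol article describes the same 200 patients in different ways.

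- Methods/design: "random allocation of approximately 200 patients who inject drugs and test positive for HCV Ab to one of two groups".
- Abstract, Methods: allocation of "approximately 200 patients who inject drugs and have chronic HCV".
- Sample size justification: the outcome is "the percentage of patients who are HCV RNA positivie and initiate treatment". The 20% control rate comes from RNA-positive patients, and 100 per group is said to detect about 17.5 points. Some 1,350 finger-stick tests are planned "in order to identify approximately 200 patients who are HCV RNA positive and will be offered treatment". The same section gives 15–20% antibody positivity among those tested and roughly 75% RNA positivity among the antibody-positive.
- Recruitment: the exclusions include "undetectable HCV RNA, a life expectancy of < 6 months".
- Intervention, simplified care (n = 100): "A complete HCV workup will be offered immediately upon a preliminary positive HCV Ab test". The RNA test is part of that workup.
- Intervention, usual care (n = 100): "Patients with a positive HCV Ab rapid finger stick test will have immediate phlebotomy performed for HCV RNA", with results given a week later.
- Statistical analysis: intention to treat, without qualification.

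**The concern.** Two hundred antibody-positive patients and 200 RNA-positive patients are different trials. On the protocol's own 75%, the first contains only about 150 patients with active infection.

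The order of events matters too. One arm starts its full on-site workup at the antibody result. The other has a blood draw and waits a week. The arm must therefore be known at the antibody result, before the laboratory reports RNA. Patients later found RNA-negative would have been randomised and would then meet an exclusion criterion. Removing them departs from intention to treat as the article states it. Keeping them puts patients who have nothing to treat into the denominator of the primary outcome.

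At stake are the denominator of the primary risk difference and the power claimed for it. There is also a possible bias. If the RNA sample is drawn after the arm is known, acceptance of it could differ by arm, and the RNA-positive subsets might then not be comparable.

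**Working it through.** **Inputs, all from the sample size section.** The test is a "two-sided, two-sample proportion test with 80% power at a significance level of 5" per cent; 100 per group; 20% versus 37.5% (20 + 17.5); RNA-positive share 75%; antibody positivity 15–20%; 1,350 tests.

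**Formula.** With n per arm, rates p1 and p2, d = p2 − p1 and p̄ their mean:

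power = Φ{ [d√n − 1.96√(2p̄(1−p̄))] / √(p1(1−p1) + p2(1−p2)) }

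The unpooled variant uses the second square root in both places.

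**Step 1: the protocol's own figure.** n = 100, p̄ = 0.2875. Then d√n = 1.750, the null term is 1.2545 and the denominator is 0.6280. (1.750 − 1.2545)/0.6280 = 0.789, so power is 78.5% (unpooled 79.6%). The detectable difference at 80% power is 17.9 points pooled, 17.6 unpooled. The stated 80% reproduces approximately when all 100 per arm are RNA-positive.

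**Step 2: 200 antibody-positive randomised, RNA-negative removed.** 200 × 0.75 = 150, or 75 per arm. d√n = 0.175 × √75 = 1.5155, and (1.5155 − 1.2545)/0.6280 = 0.416. Power is 66.1% (unpooled 67.5%). The detectable difference is 20.9 points pooled, 20.5 unpooled.

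**Step 3: 200 antibody-positive randomised, all kept.** RNA-negative patients cannot initiate, so the rates become 0.75 × 20% = 15% and 0.75 × 37.5% = 28.1%. With n = 100, d√n = 1.3125, the null term is 1.1399 and the denominator is 0.5742. Power is 61.8% (unpooled 62.8%).

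**Step 4: enough randomised for 200 RNA-positive.** 200/0.75 = 267. The planned tests give 1,350 × 0.20 = 270 antibody-positive, of whom 270 × 0.75 = 202.5 are RNA-positive. Analysing only the RNA-positive gives about 79%, as in Step 1. Analysing all 270 (135 per arm, 15% versus 28.1%) gives d√n = 1.5250 and power of 74.9% (unpooled 75.7%).

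**Step 5: yield of 1,350 tests over the stated range.**

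| Antibody positivity | Antibody-positive | RNA-positive | Tests for 200 RNA-positive |
|---|---|---|---|
| 20% | 270 | 203 | 1,333 |
| 17.5% | 236 | 177 | 1,524 |
| 15% | 203 | 152 | 1,778 |

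At 15% the plan yields about 203 antibody-positive patients, close to the count in the design section, but only about 152 who are RNA-positive.

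**Sensitivity of Step 2.** The protocol says roughly 75%. If the RNA-positive share were 70% or 80% (assumed values), pooled power would be 63.1% or 69.0%.

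**The case against.** A reader might infer that the trial is simply underpowered whichever way it is analysed. The documents do not support that. The antibody-positive count of 200 rests on one sentence. The abstract says the 200 have chronic infection, and the sample size section applies the 75% explicitly and plans its testing to find 200 RNA-positive patients. On that reading about 270 enter and power is as planned. This objection stands, and it makes the loss conditional.

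It would also go too far to say that the protocol gives no denominator. The outcome as worded in the sample size section, the source of the control rate and the undetectable-RNA exclusion all point to RNA-positive patients, and the formal analysis set may be in an SAP that is not shown. What remains is that the intention-to-treat statement does not fit an exclusion that appears to be discovered after allocation.

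The timing of randomisation is itself inferred. No sentence places it relative to the RNA draw or result, and the flow chart (Fig. 1) is not shown. The inference is strong, because the pathways differ from the antibody result onward, but it is not certain.

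On bias, RNA status is a baseline trait that allocation cannot change, and both arms are to be sampled at the antibody-positive visit. Restricting the analysis to RNA-positive patients misleads only if sampling differs by arm. The documents give no evidence that it does, so this is a risk to monitor and not a demonstrated fault.

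**Conclusion.** The contradiction holds: the design section disagrees with the abstract, the sample size section and the exclusion criteria about who is randomised. The size of the problem depends on a number that the article does not settle.

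- About 200 antibody-positive randomised: power 66–67% for 17.5 points with RNA-negative patients removed (detectable difference about 21 points), or 62–63% with all kept. The stated 80% is not delivered.
- About 267–270 randomised: about 79% on RNA-positive patients, as planned, or about 75% with everyone analysed.

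The second case needs antibody positivity at the top of the stated range, so a shortfall lies within the protocol's own assumptions. These figures assume a 75% RNA-positive share, equal in both arms, no initiation among RNA-negative patients, complete outcome data, and allocation before the RNA result.

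**What to change.** 1. Make the abstract, Methods/design, Sample size justification and Recruitment agree on whether the 200 are antibody-positive or RNA-positive. State when randomisation occurs relative to the RNA sample and result.
2. State the number randomised: about 267 antibody-positive patients for 200 RNA-positive.
3. Define the primary analysis set as all randomised patients who are RNA-positive on the baseline sample from the antibody-positive visit, analysed in the arm to which they were allocated. Report by arm how many have no RNA sample, and add a sensitivity analysis on all randomised patients.
4. If only about 200 antibody-positive patients were randomised, restate power as about 66–67% for 17.5 points, with a detectable difference of about 21 points.
5. For any patients still to be enrolled, take the existing RNA sample before the allocation is revealed. Enrolment was expected to stop in September 2023, before publication in January 2024, so this may no longer be possible. Items 1 to 4 do not depend on it.

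The cost is revised wording, slightly more analysis work and possibly a less favourable stated power. No new test is needed.
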